**GP: Information from medical records (provided by phone)**	
Survival	Mortality within the last 12 month/Date of death/Course of death
Hospital Admission	Number of Hospital Admissions/Date of Admission/Length of stay/Admission diagnosis/Emergency vs. pre-scheduled hospitalization/

Since diagnosis of heart failure will be obtained from the electronic patient records, we will double-check that the heart failure diagnosis is correct at the beginning of the telephone interview with the GP. After validating the diagnosis, the GP is asked to specify the severity level of heart failure according to New York Heart Association (NYHA) functional class. For all further information collected see Table 2.

At the 12-month follow-up assessment the patient receives a second self-administered questionnaire by mail, while data in the general practice will be extracted from the medical records of the practice and are provided by either the GP or practice staff over the phone. For further details regarding the contents of the data collection please refer to Table 2.

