**Methods/Design:**

In this multicenter, prospective, observational study 3,950 patients with HF are recruited by general practices in Germany. The patients fill out questionnaires at baseline and 12-month follow-up. At baseline the GPs are interviewed regarding the somatic and psychological comorbidities of their patients. During the follow-up assessment, data on hospitalization and mortality are provided by the general practice. Based on baseline data, the patients are allocated into three observation groups: HF patients with depression and/or anxiety recognized by their GP (P+/+), those with depression and/or anxiety not recognized (P+/−) and patients without depression and/or anxiety (P−/−). We will perform multivariate regression models to investigate the influence of the recognition of depression and/or anxiety on quality of life at 12 month follow-up, as well as its influences on the prognosis (hospital admission, mortality).

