### Study endpoints

The primary outcome of this longitudinal study is the quality of life after 12-months of follow-up. The secondary outcome is the prognosis of heart failure in terms of hospital admissions and mortality risk within the 12-month follow-up period. Group comparisons will contrast patients with depression and/or anxiety recognized by the GP (observation group 1: P(+/+)), patients with depression and/or anxiety not recognized by the GP (observation group 2: P(+/−)) and patients without depression and/or anxiety whose GPs did not diagnose any depression or anxiety (observation group 3: P(−/−)). For further information see Table 1.

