**12-MONTH FOLLOW-UP**	
**Patients: Self-administered questionnaire (by mail)**	
*All measures according to baseline; additional data:*	
Hospital admission within the last 12 month	Number of Hospital Admissions/Date of admission/Length of stay/Admission diagnosis/Emergency vs. pre-scheduled hospitalization
Change of GP	Did you change your GP within the last 12 month? If yes: How many months ago did you change your GP?

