### Data analysis

The prevalence of comorbidities in patients with HF and difficulties in the treatment of patients with HF will be analyzed by descriptive statistics. The prevalence of recognition/non-recognition of psychosocial risk factors in primary care HF patients and its impact on the study endpoints will be analysed. In a first step we will compare quality of life, hospitalisation and mortality after a 1-year follow-up period between HF patients with depression/anxiety (P+/+ and P+/−) and those without (P−/−).

In the second step we will compare quality of life, hospitalisation and mortality after a 1-year follow-up period between HF patients with depression and/or anxiety recognized by their GP (P+/+) and those with depression and/or anxiety not recognized (P+/−). We will perform multivariate regression models taking the confounding effects (e.g. comorbidity, sociodemographics, type of treatment for depression/anxiety and heart failure severity) into account.

In a third step we will compare several types of treatment for psychosocial risk factors and their potential effects on quality of life, hospitalisation and mortality after a 1-year follow-up period.

We will compare the information concerning the treatment of psychosocial risk factors gathered from patients with that gathered from GPs to evaluate potential differences (e.g. due to treatment initiated by other healthcare providers than the GP). We will re-run the analyses of the third step for information gathered from patients and for information gathered from GPs separately.

For binary outcomes (hospitalization, survival after 1 year), chi-squared tests will be used. For continuous outcomes (quality of life, survival time), t-tests or non-parametric rank tests will be used. Multivariate linear regression analyses will be performed for the total number of hospitalized days, Cox regression and Kaplan-Meier curves for time to hospitalization survival time. Multivariate linear regression will be used for quality of life.

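### Deaths are sought only in the practice's records, so deaths after a patient leaves the practice can be missed, and nothing listed for the practice call shows who has left

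*Protocol article*

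**What the plan says.** The secondary outcome in the protocol article (Study endpoints) is the "prognosis of heart failure in terms of hospital admissions and mortality risk within the 12-month follow-up period".

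- **Deaths.** Table 2 lists "Mortality within the last 12 month/Date of death/Course of death" in the 12-month block on practice records and nowhere else. The text after the table says that "data in the general practice will be extracted from the medical records of the practice and are provided by either the GP or practice staff". No registry, relative or new GP is named as a source.
- **Admissions.** The abstract states: "During the follow-up assessment, data on hospitalization and mortality are provided by the general practice". Table 2, however, also collects them from the patient at 12 months: "Number of Hospital Admissions/Date of admission/Length of stay/Admission diagnosis/Emergency vs. pre-scheduled hospitalization". The practice block has the same items.
- **Change of GP.** Only the 12-month patient questionnaire asks: "Did you change your GP within the last 12 month? If yes: How many months ago did you change your GP". The follow-up practice block lists survival and admissions only. At baseline, by contrast, the GP is asked whether they are the patient's regular GP, and patients not regularly attending the practice are excluded.
- **Analysis.** Data analysis states: "For binary outcomes (hospitalization, survival after 1 year), chi-squared tests will be used". It also names "Cox regression and Kaplan-Meier curves for time to hospitalization survival time". It gives no rule for patients who have left the practice.
- **Linkage.** Under Data protection, the allocation key is deleted once follow-up data entry is complete, and the data are anonymous from then on.

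**The concern.** A practice record that shows no death can mean that the patient is alive, or that the patient has left and the practice no longer knows. The listed follow-up items do not tell these apart. The one item that could, the question on GP change, goes only to patients who can return a questionnaire at 12 months. It therefore fails for precisely those who left and then died, and also for those who left and did not respond.

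If such patients are recorded as having no event, absolute risks of death and, for non-responders, of admission come out too low. If leaving the practice differs between P+/+ and P+/−, the comparison of recognised with unrecognised depression or anxiety is distorted as well. The protocol itself asks whether recognition is associated with aspects of care such as contact frequency, so a link between recognition and attachment to the practice is conceivable. Once the key is deleted, vital status cannot be recovered, and no analysis can censor at a last-contact date that was not collected.

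**Working it through.** **1. Who is affected.** Setting the Table 2 items against the possible cases:

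| Patient at 12 months | Death status | Admissions |
|---|---|---|
| Still attends | Practice record | Practice record, plus patient report if returned |
| Left, returned questionnaire | Known alive | Patient report with dates; month of GP change known |
| Left, did not return, alive | Unknown, and not flagged as unknown | Practice record up to departure only |
| Left, then died | Missed unless the old practice hears of it | Practice record up to departure only |

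The gap lies in the last two rows. Returned questionnaires recover none of the deaths in the last row.

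**2. Inputs.** The document gives no switching rate, event rate or hazard ratio, so there is no stated figure to reproduce. From Sample size calculation: 10,973 × 0.40 × 0.90 = 3,950 at baseline; × 0.20 = 790 with depression and/or anxiety; split 75:25, about 592 P+/+ and 198 P+/−. Planned loss to follow-up is 15%, or 0.15 × 790 ≈ 119 patients. If that loss is questionnaire non-return, GP change is unknown for them.

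Assumptions: share switching *s* = 3-10%; switching spread evenly over the year, so half the year is uncovered on average; no later death reaches the old practice; mortality in switchers is *k* times that in others, with *k* = 1 or 3.

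**3. Share of deaths missed** = 0.5·s·k / [(1 − s) + s·k]

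- s = 0.03, k = 1: 0.015 / 1.00 = 1.5%
- s = 0.03, k = 3: 0.045 / 1.06 = 4.2%
- s = 0.10, k = 1: 0.050 / 1.00 = 5.0%
- s = 0.10, k = 3: 0.150 / 1.20 = 12.5%

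With an assumed 10% one-year mortality there are 79 deaths among 790 patients. Then 79 × 0.015 ≈ 1.2 to 79 × 0.05 ≈ 4.0 are missed at k = 1, and up to 79 × 0.125 ≈ 9.9 at k = 3.

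**4. Effect on the P+/− to P+/+ risk ratio** = ratio of the shares of deaths captured

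- Equal switching and equal k: 1.00, no bias.
- 10% in P+/−, 3% in P+/+: 0.950 / 0.985 = 0.964 (k = 1); 0.875 / 0.958 = 0.914 (k = 3).
- The reverse split: 1 / 0.964 = 1.04 (k = 1); 1 / 0.914 = 1.09 (k = 3).

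**5. Scale against sampling error.** At 10% mortality, about 59 and 20 deaths. SE of the log risk ratio = √(1/59 − 1/592 + 1/20 − 1/198) ≈ 0.245, so the 95% interval extends by a factor of exp(1.96 × 0.245) ≈ 1.6 each way.

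**The case against.** A reader might infer that every patient who changes GP counts as event-free for the rest of the year, on both secondary outcomes, and that this makes non-recognition look safer than it is. The documents do not support that.

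- Admissions do not come from practice records alone. Patients report them with dates, so a responder who has switched still has admission data after the change. The abstract's shorter statement does not override Table 2.
- A returned questionnaire proves survival, so a full year at risk is right for a responding switcher.
- No rule says that leavers are scored as having no event. Data analysis is silent, and Cox and Kaplan-Meier methods accommodate censoring. Censoring and source-priority rules may stand in a full protocol or analysis plan that is not shown, and their absence from an article is no error.
- Neither the size nor the direction of a group difference is documented. Reversing the assumed split reverses the bias, and equal switching removes it from the ratio.
- The design selects attached patients (regular attenders with a contact in the last six months), which may keep switching low.
- Even the unfavourable scenario shifts the risk ratio by less than its sampling error, and the primary outcome, quality of life, does not depend on practice records.

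All of this stands. It could also be said that Table 2 lists topics rather than a call script. But the table does place the GP-change item, with its timing, in the patient block and not in the practice block. That is a choice of data source, and an analysis plan cannot make good a date that was never collected.

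**Conclusion.** The point holds in a limited form. Death ascertainment rests on the practice alone, and leaving the practice is visible only through a questionnaire that those who leave and then die cannot return. Among leavers who do not return it, deaths and later admissions can be missed without being recognised as missing. Survival of responders is unaffected.

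Under the stated assumptions, 1.5-5% of deaths are missed with equal mortality and about 4-12% with threefold mortality in switchers. These lie at the upper end for each scenario, because the old practice will hear of some deaths. Absolute risks would be too low; bias in the P+/+ v P+/− contrast is possible but of unknown direction. It is a minor-to-moderate point, confined to the secondary outcomes, and worth acting on because it is cheap to fix and cannot be repaired after the key is deleted.

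**What to change.** 1. **Data collection.** In the existing 12-month practice call, ask whether the patient still attends the practice and the date of last contact. Do this, and resolve open vital status where possible, before the allocation key is deleted.
2. **Leavers who did not return the questionnaire and whose vital status is unknown.** Censor at last contact rather than record no event. Take 1-year risks from Kaplan-Meier estimates instead of raw proportions compared by chi-squared test.
3. **Responders who changed GP.** Treat the return as proof of survival, and use their self-reported admissions for the time after the change.
4. **Sensitivity analysis for mortality.** Censor all leavers at departure, responders included. Rule 3 keeps full follow-up for leavers who survive and respond, while those who die after leaving are censored, so some downward bias remains under rules 2 and 3 alone.

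Cost: two short items in a call already planned, some analysis wording, and slightly less observed person-time. Censoring at departure still assumes that leaving is unrelated to prognosis given the covariates, which should be stated.

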### Recognition of depression and anxiety

A sub-study is performed by the University of Göttingen Medical Center, which is not involved in the main study. The aim of this sub-study is to identify appropriate cut-points and combinations of established self-rating scales for depression and anxiety in primary care patients with heart failure. For this purpose, a subsample of 190 patients with symptomatic heart failure completes the Hospital Anxiety and Depression Scale (HADS) [29,30], Patient Health Questionnaire 9-item Subscale Depression (PHQ-9) [26-28] and Patient Health Questionnaire 7-item Subscale Generalized Anxiety Disorder Assessment (GAD-7) [33-35], as well as selected items from PROMIS Depression and Anxiety scales [31,32], and undergoes the Structured Clinical Interview for DSM-IV (SCID) [47]. The SCID is a structured one-hour face-to-face diagnostic interview by a trained psychologist with a patient. It is the reference standard for the diagnosis of depression and anxiety disorders in research projects [48]. In this study SCID interviews are performed by psychologists (blind to patients’ self-ratings), to identify the relative value and optimal clinical cut-points for the identification of primary care patients with HF and comorbid depression or anxiety disorders. Different cut-points on the self-rated PHQ-9, GAD-7, and HADS are compared by Receiver Operating Characteristics for the detection of different classes of SCID-based diagnoses. If appropriate, exploratory analyses are attempted to optimise case finding algorithms based on combinations of the self-rating scales or their individual items. Previous research has shown that such analyses are feasible with the designated sample size for the sub-study [49,50].

In the main study, the case finding algorithm (identified in the SCID sub-study) is applied on the information given in the baseline questionnaire. Therefore, the questionnaire includes the same self-administered instruments as used in the sub-study (HADS, PHQ-9 and GAD-7, PROMIS Depression and Anxiety scales). Depending on the algorithm from the sub-study, the patients are classified as patients with depression and/or anxiety or patients without depression and/or anxiety. Due to the work load, we do not interview the GPs of 25% of the patients without depression and anxiety by phone. Therefore, for each practice 75% of all patients without depression and/or anxiety (group P-) are randomly selected for telephone interviews with the GP and assigned to the observation group 3 (P-).

After baseline assessment, GP interviews will be available for each patient assigned to one of the three observation groups. For further detail see Figure 1.

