### Expected implications for health policy

Public health planners are in need of numbers such as frequency of depression and anxiety as well as frequency of different treatment options substantiating the decision process of resource allocation. For the health planners we will describe the frequency of depression and/or anxiety missed by GPs and the potential treatment gap.

Such a treatment gap with respect to psychosocial problems in HF patients is currently unproven but needs to be assumed if preliminary findings are transferred onto the general population. If so, more resources should be spent on investigating effective treatments.

For these investigations the differential effects of correctly acknowledged and missed depression and/or anxiety on outcome, also in comparison to the outcome of subjects without depression and/or anxiety, will help to better understand how health care for HF patients needs to be improved and which treatment might be effective. We will be able to present evidence to what extent the recognition of depression and/or anxiety through screening for depression and anxiety is mandatory for HF patients, as already recommended in clinical guidelines.

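### Screen-positive status is treated as the diagnosis, so GP recognition is understated and the missed share overstated if GPs flag false positives less often than true cases

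*Protocol article*

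**What the plan says.** The protocol article (Recognition of depression and anxiety) describes "a subsample of 190 patients with symptomatic heart failure" who complete the self-rating scales and undergo the SCID. Of the SCID it says: "It is the reference standard for the diagnosis of depression and anxiety disorders in research projects". Cut-points on the scales "are compared by Receiver Operating Characteristics for the detection of different classes of SCID-based diagnoses".

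In the main study there is no diagnostic interview. Instead, "the case finding algorithm (identified in the SCID sub-study) is applied on the information given in the baseline questionnaire", and "Depending on the algorithm from the sub-study, the patients are classified as patients with depression and/or anxiety or patients without depression and/or anxiety". Screen-positive patients whose GP reports depression or anxiety form P+/+, and those whose GP does not form P+/−. Both groups are defined as patients who have the condition. GPs are interviewed about all screen-positives, whereas "for each practice 75% of all patients without depression and/or anxiety (group P-) are randomly selected" for interview. Screen-negative patients whom the GP calls positive are to be considered separately.

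Data analysis reports the prevalence of recognition and non-recognition and, in step 2, compares P+/+ with P+/− on quality of life, hospitalisation and mortality. The Discussion (Expected implications for practice) presents the result as the number of patients who have the conditions, and the next subsection states that "we will describe the frequency of depression and/or anxiety missed by GPs and the potential treatment gap".

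**The concern.** A screen with specificity below 1 puts some patients without a SCID disorder among the cases. If GPs flag these patients less often than true cases, most of them go to P+/−, and a correct GP judgement is counted as a miss. Two results are affected.

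- **Recognition rate and treatment gap.** These are offered to GPs and health planners as a description of care.
- **Step 2 comparison on the primary outcome.** P+/− would hold many more non-cases than P+/+. Unrecognised patients could then look better off because fewer of them are ill, whatever recognition does.

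**Working it through.** **The plan's own figures.** Sample size calculation states 672 patients (504 recognised, 168 not) for a 5-point EQ-VAS difference, 80% power and α = 0.05. The SD is not stated. With SD 20, two-sided, 3:1 allocation: n = (1 + 1/3) × (1.960 + 0.842)² × 20²/5² ≈ 167.4, so 168 and 504, total 672. Then 672/0.85/0.20 = 3,953 (stated 3,950) and 3,950/0.90/0.40 = 10,972 (stated 10,973). These figures are not in dispute. The prevalence and recognition rate behind them are used below as the assumed truth.

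**Inputs**
- Prevalence π = 0.20 and GP recognition of true cases r = 0.75 (Sample size calculation).
- Sensitivity Se 0.80-0.90 and specificity Sp 0.80-0.95: assumed, because the article gives none.
- GP-positive rate in non-cases f = 0.05-0.20: assumed.

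**Formulas**
- Apparent prevalence = Se·π + (1 − Sp)(1 − π)
- PPV = Se·π / apparent prevalence
- Apparent recognition = PPV·r + (1 − PPV)·f
- Non-case share of P+/− = (1 − PPV)(1 − f) / [PPV(1 − r) + (1 − PPV)(1 − f)]

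Apparent recognition equals r only if PPV = 1 or f = r. For f below r it is too low.

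**Worked example, Se = Sp = 0.85, f = 0.10**
- True positives 0.85 × 0.20 = 0.17; false positives 0.15 × 0.80 = 0.12; apparent prevalence 29%.
- P+/+ = 0.17 × 0.75 + 0.12 × 0.10 = 0.1275 + 0.012 = 0.1395.
- P+/− = 0.0425 + 0.108 = 0.1505.
- Apparent recognition 0.1395/0.29 = 48%, so 52% appear missed, against a true 25%.
- Non-cases are 0.108/0.1505 = 72% of P+/−.

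**Range (f = 0.05-0.20)**

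| Se | Sp | Apparent prevalence | Apparent recognition | Non-cases in P+/− |
|---|---|---|---|---|
| 0.80 | 0.80 | 32% | 40-48% | 76-79% |
| 0.85 | 0.85 | 29% | 46-52% | 69-73% |
| 0.80 | 0.95 | 20% | 61-64% | 44-49% |
| 0.90 | 0.95 | 22% | 62-65% | 42-46% |

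Over the whole grid, apparent recognition is 40-65%, the apparent missed share 35-60% and apparent prevalence 20-34%.

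**Step 2.** In the worked example true cases are 0.1275/0.1395 = 91% of P+/+ and 0.0425/0.1505 = 28% of P+/−, a difference of 0.63. If recognition had no effect, the groups would still differ by 0.63 times the EQ-VAS gap between true cases and false positives. A gap of 5/0.63 ≈ 8 points would alone produce the plan's 5-point target difference. At Se 0.80, Sp 0.95, f = 0.10 the shares are 0.12/0.124 = 97% and 0.04/0.076 = 53%, a difference of 0.44, so the gap would have to be about 11 points.

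**Precision of a correction.** At 20% prevalence, 190 patients include about 38 SCID cases and 152 non-cases. The 95% half-width is 1.96 × √(0.85 × 0.15/38) ≈ 11 points for sensitivity and, with 152, about 6 points for specificity. Simulating this uncertainty in the worked example gives corrected prevalence of about 12-27% and corrected recognition from about 61% up to the 100% ceiling.

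**The case against.** The strongest defence has four parts.

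**The article is condensed.** Its analysis section does not exclude a correction, weights or internal validation, and an unseen analysis plan may contain them. This stands for the details. A reader might infer that the algorithm's accuracy is certainly optimistic because it is tuned and assessed in the same 190 patients. The article does not say how accuracy will be estimated, so that would be an inference from silence. The case definition, the group labels and the promised claims are, however, fixed in the article itself.

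**Recognition is symptom-based.** The GP is first asked whether the patient displays symptoms, and only then whether they amount to a diagnosis. Screen-positive patients without a SCID disorder may have sub-threshold symptoms, so f among them could be well above 0.20. With f = 0.40 and Se = Sp = 0.85, apparent recognition is (0.1275 + 0.048)/0.29 = 60.5%. This reduces the bias but does not remove it.

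**A correction can overshoot.** The simple correction assumes that screen and GP err independently given SCID status, although both respond to the same symptoms. Suppose GPs flag 40% of screen-positive and 7% of screen-negative non-cases. The independence correction then solves 0.17r + 0.12f = 0.1755 and 0.03r + 0.68f = 0.0701, giving r ≈ 99% against a true 75%. That is further from the truth than the raw 60.5%. This stands, and it is why a corrected figure should not replace the raw one.

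**The 75% sampling leaves the main rates untouched.** Depression/anxiety prevalence uses all returned questionnaires, and recognition is computed within screen-positives, all of whom are interviewed. This also stands. Weights matter only for pooled GP-interview descriptives: screen-positives are 790/(790 + 2,370) = 25% of interviews against 20% of the cohort, so a 10-point difference between groups shifts a pooled rate by 0.5 points.

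**Conclusion.** The point holds for recognition, the missed share and the step 2 comparison. It rests on two conditions: specificity below 1, and GPs flagging false positives less often than true cases. Under the plan's 20% and 75% and the assumed ranges, apparent recognition is 40-65% and non-cases are 42-79% of P+/−. The sizes are illustrative, because the article gives no sensitivity, specificity or GP false-positive rate.

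Two stronger conclusions that a reader might draw are not supported. Prevalence is not necessarily inflated: at Se 0.80 and Sp 0.95 false positives and false negatives cancel and it stays at 20%, although recognition is still too low. Nor is P+/− always mostly non-cases: in that same setting the share is 44-49%.

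The plan should be changed, but the remedy is one of labelling and sensitivity analysis. The design can stay as it is.

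**What to change.** 1. Report the raw figures as screen-positive prevalence and GP agreement among screen-positives, and reword the Discussion so that screen-positive, GP-negative patients are not called missed cases.
2. As a sensitivity analysis, add prevalence and recognition corrected with the sub-study's sensitivity and specificity, carrying their sampling uncertainty into the intervals.
3. For recognition, use the screen-by-GP table with screen-negatives weighted by 1/0.75. Show results under conditional independence and over a stated range of dependence between screen and GP errors.
4. Repeat step 2 at a higher-specificity cut-point as a sensitivity analysis.
5. Weight pooled GP-interview descriptives, such as comorbidity prevalence, by 1/0.75 for screen-negatives. This is minor.

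**Cost.** Extra analysis of data already being collected. The corrected intervals will be wide (about 38 expected SCID cases), and the dependence assumption cannot be tested in this study. The sub-study covers symptomatic heart failure only, whereas Recruitment accepts any documented heart failure diagnosis, so the error rates may not transfer fully. The report should say so.
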